## Abstract

**Introduction:**

Sedentary behaviour (sitting or lying during waking hours without being otherwise active) is strongly associated with adverse health outcomes, including all-cause, cancer and cardiovascular mortality in adults. Stroke survivors are consistently reported as being more sedentary than healthy age-matched controls, spending more hours sedentary daily and sustaining longer unbroken bouts of sedentary time. An evidence-based and clinically feasible intervention (‘Get Set Go’) was developed. A pragmatic definitive trial to evaluate Get Set Go was planned; however, due to the unprecedented effects of the COVID-19 pandemic on National Health Service (NHS) services this study was reduced in size and scope to become an external pilot trial. We report the protocol for this external pilot trial, which aims to undertake a preliminary exploration of whether Get Set Go is likely to improve ability to complete extended activities of daily living in the first year post-stroke and inform future trial designs in stroke rehabilitation.

**Methods and analysis:**

This study is a pragmatic, multicentre, two-arm, external pilot cluster randomised controlled trial with embedded process and economic evaluations. UK-based stroke services will be randomised 1:1 to the intervention (usual care plus Get Set Go) or control (usual care) arm. Fifteen stroke services will recruit 300–400 stroke inpatient and carer participants, with follow-up at 6, 12 and 24 months. The proposed primary endpoint is stroke survivor self-reported Nottingham Extended Activities of Daily Living scale at 12 months. Endpoint analyses will be exploratory and provide preliminary estimates of intervention effect. The process evaluation will provide valuable information on intervention fidelity, acceptability and how it can be optimised.

**Ethics and dissemination:**

The study has been approved by Yorkshire and The Humber – Bradford-Leeds Research Ethics Committee (Ref: 19/YH/0403). Results will be disseminated through journal publications and conference presentations.

**Trial registration number:**

This trial was registered prospectively on 01 April 2020 (ISRCTN ref: ISRCTN82280581).

Strengths and limitations of this studyAn external pilot cluster randomised control trial design enables the collection of feasibility and acceptability data to inform future trial designs in stroke rehabilitation.The comprehensive set of outcome measures collected will ensure any potential impacts of the intervention on meaningful outcomes for stroke survivors (eg, short-term and long-term changes to activities of daily living, quality of life and well-being) are captured.The study will collect objective measures of sedentary behaviour (using activity monitors), which to date have been infrequently assessed in post-stroke rehabilitation trials with longer-term outcomes up to 24 months.The inclusion of an embedded process evaluation (reported separately) will provide valuable information on the intervention fidelity, acceptability and how it can be optimised.The inclusion of a nested Study Within A Trial (reported separately) will enable the systematic evaluation of whether a video animation could enhance participant understanding and subsequently uptake, engagement and compliance with the intervention and thus inform how best to implement the intervention in practice.

## Introduction

### Background and rationale

There are clear associations between sedentary behaviour in the general population and increased risk of adverse health outcomes, including all-cause, cancer and cardiovascular mortality, and incidence of cardiovascular disease, cancer and type 2 diabetes.^1 2^ Sedentary behaviour is defined as any waking behaviour characterised by low energy expenditure ≤1.5 metabolic equivalent of task while in a sitting, lying or reclining posture,^3^ and importantly differs from physical inactivity, which refers to achieving insufficient levels of moderate-to-vigorous physical activity (MVPA). An individual may therefore not reach the recommended levels of physical activity (PA) yet spend little time sitting, whereas others may be physically active for short bursts (eg, running for an hour), but spend prolonged periods sitting. Increasing MVPA can offset some of the detrimental effects of sedentary behaviour, although high levels are required (ie, >300 min/week).^1^

Stroke survivors are more sedentary than other population groups.^4–6^ Longitudinal studies;^7^ systematic reviews^8 9^ and observational studies^6^ reported that stroke survivors are considerably more sedentary (in hours per day) and have longer unbroken bouts of sedentary time than healthy age-matched controls. Sedentary behaviour does not improve over the first year after stroke^7^ and appears independent of the level of functional recovery,^7 8 10^ with physical ability only having a small influence on time spent sitting in people living at home 6 months after stroke.^10^ The high amount of reported sitting time by stroke survivors is likely to generate a range of negative outcomes. Epidemiological studies^11^ place them in the highest quartile for cardiovascular risk. For a stroke survivor, increased sedentary behaviour may thus result in a ‘perfect storm’ of deteriorating physical function and health-related quality of life, coincident with rising risks for cardiovascular disease.

There has been increasing focus in international public health guidance on reducing sedentary behaviour, particularly for those with disabilities, such as those resulting from stroke, as for many it may be a more achievable target than increasing PA.^12^ Short brief activity breaks throughout the day may be as effective as a continuous 30-min or 60-min bout of exercise (summarised in a study by Dempsey *et al*
13). Experimental studies (primarily short-term, laboratory-based work) provide supporting evidence of the positive effect on metabolic outcomes of breaking up sitting time with short bursts of activity in standing^14 15^ and reducing stroke risk.^16^

Furthermore, the potential benefits of reducing sedentary behaviour reach beyond those relating to mortality and cardiovascular risk. Indeed, sedentary behaviour has been identified as a modifiable behaviour to enhance physical function^17^ and maintain muscle strength, thus potentially supporting the ability to undertake activities of daily living (ADLs).^17–19^ These benefits are important not just for stroke survivors themselves but may also extend to their carers; a recent systematic review identified post-stroke disability as the biggest predictor of carer burden.^20^ Improved physical function in stroke survivors may thus reduce carer strain. Sedentary behaviour has also been identified as important in relation to mental health, cognitive outcomes and health-related quality of life.^21^

To address the challenge of reducing sedentary behaviour after stroke, we embarked on a programme of work (RECREATE) to develop an evidence-based and clinically feasible intervention to reduce/break up sedentary behaviour in stroke survivors. Intervention development was informed by systematic reviews and qualitative work, and underpinned by behaviour change theory (the Behaviour Change Wheel^22^). The final intervention (‘Get Set Go’) was developed using co-production methods.^23^ A logic model of intended intervention mechanisms and outcomes was also constructed, and implementation strategies were refined using a case study approach. The intervention is intended to begin early after stroke (in the inpatient setting) and continue into the community, and is designed to fit into existing rehabilitation and recovery pathways.

This protocol represents the final stage in the RECREATE programme, which aims to evaluate the developed intervention in a sample of stroke survivors and carers. A large definitive multicentre cluster randomised controlled trial (cRCT) with 34 stroke services each recruiting 34 participants was initially planned, with the aim of evaluating the effectiveness and cost-effectiveness of the developed intervention. However, due to issues related to the worldwide COVID-19 pandemic, site recruitment was slower than expected. As a result, in spring 2022, following meetings with the Programme Steering Committee (PSC) and a stakeholder meeting convened by the funder (National Institute for Health and care Research (NIHR)), a decision was taken with the funder to amend the protocol to reduce the trial in size and scope to become an external pilot trial.

### Objectives

The primary objective is to undertake a preliminary exploration of whether the intervention (Get Set Go) is likely to improve the ability to complete extended activities of daily living (EADLs) in the first year after stroke. A key secondary objective is to explore whether the intervention is likely to reduce sedentary behaviour. Other secondary objectives are to:

Explore core resource use and costs associated with delivering the intervention including impacts on wider care.Explore whether the intervention reduces cardiovascular risk factors.Explore whether the intervention reduces disability.Explore whether the intervention improves health and well-being outcomes, such as health-related quality of life and mental well-being.Explore whether the intervention reduces carer strain.Explore and understand implementation of the intervention, including intervention adherence, compliance, the process, benefits and challenges.Explore and understand how the intervention is experienced and understood by recipients and providers.Explore potential moderators and mediators of the intervention effect.

Objectives 1−5 will be addressed in the cRCT. Additional objectives addressed in the cRCT relate to gathering feasibility and acceptability data to inform future trial designs in stroke rehabilitation. Objectives 6−8 will be addressed in an embedded mixed-methods process evaluation (protocol reported separately), which will develop an understanding of how the intervention is implemented, understood and experienced by both providers and recipients.

## Methods

### Design

This trial is a pragmatic, multicentre, two-arm external pilot cRCT. The Get Set Go intervention will be delivered alongside usual care at the level of the stroke service (ie, cluster). The cluster design will reduce between-group contamination. Eligible stroke services will be randomised on a 1:1 basis to the two arms of the trial: either intervention (usual care plus Get Set Go) or control (ie, usual care). All stroke survivors in services allocated to the intervention arm will receive Get Set Go; however outcomes will only be measured for those who consent to trial participation.

### Settings

The trial will be conducted in up to 15 National Health Service (NHS) stroke services across the UK. A stroke service is defined as an acute and/or rehabilitation stroke unit with a linked community service over a defined geographical area. Service eligibility criteria are detailed in table 1.

**Table 1 T1:** Stroke service eligibility criteria

Inclusion criteria	Exclusion criteria
Both the inpatient and community service agree to participate.	Previous participation in research leading to the development of the intervention.
Availability of research staff to undertake participant recruitment.	Currently implementing/intending to implement similar interventions within trial duration.
Agreement that recruitment targets are feasible/acceptable (considering patient throughput).	Early supported discharge (ESD) (or community if no ESD) waiting list >4 weeks post-discharge.
The intervention can be feasibly implemented (if so randomised).	

### Recruitment

Three to four hundred stroke survivors and carers will be recruited to participate. Eligibility criteria are outlined in table 2. Carer involvement is not a requirement for stroke survivor inclusion.

**Table 2 T2:** Stroke survivor and carer eligibility criteria

	Inclusion criteria	Exclusion criteria
Stroke survivor	Aged ≥16 years at time of stroke.	Receiving palliative care.
	Clinical diagnosis of new or recurrent ischaemic or haemorrhagic (excluding subarachnoid haemorrhage) stroke.	Due to be discharged outside the defined geographical area of the associated community service(s) participating in the trial.
	Requires manual contact of no more than one person to stand to prevent falling (manual contact consists of continuous or intermittent light touch to assist balance or coordination, that is, not to support body weight).	
	Plan to live in the community post-discharge.	
	Informed consent/consultee declaration is provided.	
Carer	Aged ≥16 years.	Stroke survivor does not consent to participate.
	Family member or friend regularly engaging with a stroke survivor participant (≥once per fortnight).	
	Provide informed consent.	

Conversations with interested stroke services began in October 2019 in preparation for the study starting in December 2019. Recruitment of stroke survivors and carers started in January 2021. The study is projected to complete recruitment by the end of April 2023 with the follow-up due to complete in April 2024. The end of the study is defined as the date the last participant’s data item is collected.

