#### Sample size

As previously described, our original plan for a large definitive multicentre RCT was reduced in size and scope, due to issues related to the COVID-19 pandemic. We aim to recruit 300–400 participants across 15 stroke services. This revised sample size is based on the anticipated recruitment rate within the remaining time available in the funded programme, estimated at two participants per month per site. As intervention effectiveness will not be evaluated and all analyses will be of an exploratory nature, the study does not have a formal power calculation.

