### Health economic analysis

The embedded health economic evaluation will assess resource use, costs and outcomes to inform data collection approaches for a future definitive trial, specifically:

Alternative approaches to measuring hospital resource use (routine records vs self-report);A short (6-month) versus medium (12-month) versus longer (24-month) analytical time horizon; andA reduced list (narrow perspective) evaluation based on routine data versus long list (comprehensive perspective) evaluation incorporating self-reported data.

Two perspectives will be considered, as relevant to the analyses: health/social care (including institutionalisation), and a wider perspective covering health/social care (including institutionalisation) plus informal care given the significance of such inputs for this patient group.

Resource use data will be collected using a combination of NHS England secondary care data and self-report approaches via the CSRI. Resource use will be combined with relevant unit costs, using within-programme estimates related to the intervention, national estimates for other health and social care resources and both an opportunity cost and replacement cost approach in turn for informal care. Total costs will be computed for each individual according to each of the estimation alternatives set out above. Differences between the two trial arms will be compared using bootstrap regression methods due to the expected skewness in data distributions.

Exploratory cost-effectiveness analyses will combine total costs with the primary outcome and with QALY gains estimated by attaching relevant general population utility weights to EQ-5D-5L health states at each time point. Uncertainty will be analysed using cost-effectiveness planes and cost-effectiveness acceptability curves. Sensitivity analyses will explore the potential impact on cost-effectiveness from different implementation/costing scenarios. This would better inform future trial design and implementation discussions. Other relevant sensitivity analyses will be determined during the study and will be specified in the analysis plan prior to analyses.

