### Adverse event reporting and harms

Adverse events (AEs) such as falls and musculoskeletal injuries represent an inherent consequence of an active rehabilitation process and therefore cannot be entirely avoided. Similarly, in this patient population, acute illness resulting in hospitalisation, new medical problems and deterioration of existing medical problems are expected. In recognition of this, events fulfilling the definition of an AE or SAE will not be reportable in this study unless they result from administration of any research procedures and therefore fulfil the definition of an unexpected and related SAE, or if they constitute one of the following: death, hospital readmission, institutionalisation, treatment on an emergency outpatient basis or emergency department attendance. The latter will be reported at 6, 12 and 24 months post-registration follow-up by the clinical research team using health and social care records. All related/unexpected SAEs occurring from the date of consent up to 24 months post-registration must be reported within 24 hours of the clinical research staff becoming aware of the event. All related/unexpected SAEs will be reviewed by the CI and subject to expedited reporting to the sponsor and the main Research Ethics Committee (REC) by the CTRU on behalf of the CI within 15 days.

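### Follow-up is due to end in April 2024, so only participants registered by about April 2022 can supply the 24-month data that the article schedules for everyone

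*Protocol article*

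**What the plan says.** The Recruitment section fixes the calendar. It says "Recruitment of stroke survivors and carers started in January 2021" and then "The study is projected to complete recruitment by the end of April 2023 with the follow-up due to complete in April 2024". It adds: "The end of the study is defined as the date the last participant’s data item is collected".

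The rest of the article sets a 24-month schedule without saying that it covers only some participants:

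- The abstract (Methods and analysis) says "Fifteen stroke services will recruit 300–400 stroke inpatient and carer participants, with follow-up at 6, 12 and 24 months".
- Endpoints lists most secondary endpoints, and the carer strain endpoint, at 6, 12 and 24 months after registration. Table 3 has a 24-month column filled for nearly all follow-up assessments.
- Procedure sends assessment packs at all three time points, with activity monitors and cardiovascular risk markers also collected at follow-up.
- Health economic analysis compares short and medium horizons with a "longer (24-month) analytical time horizon", and says that total costs are computed for every individual under each of the alternatives listed.
- Statistical analysis applies all analyses and summaries to an intention-to-treat population made up of everyone registered.

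The Sample size section bases the target of 300–400 participants in 15 services on the recruitment rate expected in the remaining funded time, "estimated at two participants per month per site".

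**The concern.** The two statements cannot both hold for all participants. Anyone registered in the last year of recruitment reaches the planned close before the 24-month visit falls due. That absence is administrative and fixed by registration date. It is not loss to follow-up, yet nothing in the readable text separates the two. The reasons given for missing assessments are examples such as death or moving away, and planned truncation is not among them.

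If the text is followed as written, the 24-month summaries would mix people who were never due an assessment with people who were due one and did not provide it. A 24-month completion rate calculated over all registrants would then understate retention, which matters in a pilot meant to supply feasibility data.

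The economic comparison of 6, 12 and 24-month horizons is also exposed. The 24-month data can come only from early registrants, in whichever services had opened by then, whereas the 6 and 12-month data come from everyone. A difference between horizons would be partly a difference between calendar periods and services.

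**Working it through.** **Inputs.** Recruitment start January 2021, recruitment end April 2023 and follow-up end April 2024 (Recruitment); target 300–400, 15 services, 2 per month per site (Sample size); redesign in spring 2022 (Background and rationale). Month-by-month accrual is not given.

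**The plan's own target.** At full capacity the rate is 15 × 2 = 30 per month. Then 300 / 30 = 10 months and 400 / 30 = 13.3 months. The 12 months from May 2022 to April 2023 give 30 × 12 = 360, inside the target range. The whole window at that rate would give 30 × 28 = 840. The target is therefore consistent with about a year of full-capacity recruitment, and not with that rate over the full window.

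**Follow-up available to the last recruit.** April 2023 to April 2024 = 12 months. This reaches the 12-month primary and key secondary endpoints but not 24 months.

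**Latest registration that can reach 24 months.** April 2024 − 24 months = April 2022. To give the last recruit 24 months, follow-up would have to run to April 2023 + 24 months = April 2025, which is 12 months past the stated end.

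**Recruitment months on each side of that date.** January 2021 to April 2023 is 28 months. January 2021 to April 2022 is 16 months, which leaves 12.

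**Share of participants who cannot reach 24 months, by assumed accrual pattern:**

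| Assumption | Can reach 24 months | Cannot |
|---|---|---|
| Even accrual over 28 months | 16/28 = 57% (171 of 300; 229 of 400) | 12/28 = 43% (129 of 300; 171 of 400) |
| Linear ramp, month i weighted by i | (1+…+16)/(1+…+28) = 136/406 = 33% | 270/406 = 67% |
| All 15 services at 2 per month from May 2022, total of 400 | 40 of 400 = 10% | 360 of 400 = 90% |

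The third row is a limiting case, not an estimate. It needs every service open for the whole final year and only 40 registrations in the 16 months before.

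**The case against.** The strongest reply is that this is an external pilot with no power calculation and only exploratory analyses, and that its primary and key secondary endpoints are at 12 months, which the last recruit can reach. The article condenses a fuller protocol, the participant timeline (Figure 1) is not shown, and a restriction could stand in either. Analysis-set detail is also commonly left to the analysis plan. This limits the seriousness of the point. It does not remove the conflict, because the article states both the dates and the unrestricted schedule, and nothing readable reconciles them.

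A reader might infer more than the document supports:

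- **That 12-month primary data are cut off at closure.** April 2024 is a projection to the month. The end of the study is defined by the last data item, missing data are sought until the trial is at analysis, and final analysis waits for all available data. No hard cut is stated.
- **That 24-month values will be imputed for everyone.** Multiple imputation is conditional wherever it appears, used if or where appropriate. The text does not commit to imputing assessments that were never due. It simply does not rule it out.
- **That reported 24-month retention will be wrong.** No retention denominator is defined, so this is a risk and not a stated error.
- **That the safety window contradicts the dates.** Events "occurring from the date of consent up to 24 months post-registration" can be read as a maximum, compatible with shorter observation of later recruits.
- **That almost nobody can reach 24 months.** Recruitment began in January 2021, the number of services is given as up to 15, site recruitment was slow, and the article does not say whether the 300–400 includes people already registered.

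**Conclusion.** The point holds for the 24-month outcomes only. On the stated dates, participants registered after about April 2022 cannot provide 24-month data, while the 24-month secondary and carer endpoints, Table 3, the follow-up procedure and the 24-month economic horizon are written for all participants. The April 2022 limit follows from the dates alone. The share affected rests on assumed accrual: about 43% if even and about 67% under a linear ramp. It is higher if most of the target was recruited after the redesign, with 90% as a limiting case for a total of 400. The primary and key secondary endpoints at 12 months stand.

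**What to change.** Reconcile the passages in one of two ways: state that 24-month follow-up applies only to participants registered by April 2022, or correct the follow-up end date. Covering everyone would mean April 2025.

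If 24-month follow-up is restricted:

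- Use that subset as the denominator for all 24-month summaries, models, retention figures and cost and QALY results.
- Class later registrants as not due at 24 months, not as missing, and do not impute assessments that were never due.
- Make the 6 v 12 v 24-month horizon comparison within the same subset, so that the horizons differ in length and not in who is included. The 6 and 12-month results for all participants are reported as already planned.

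The restriction costs a few sentences in the protocol and analysis plan. Its downside is that the 24-month results become explicitly those of a smaller group of early recruits, possibly from fewer services, and must be described as such. Moving the end date instead would add a year of follow-up.
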